## Abstract

**Introduction:**

Maternal expulsive force is a key determinant of fetal head descent during the active second stage of labour. Pushing is most effective when abdominal muscle contraction is synchronised with relaxation of the levator ani muscle, thereby widening the pelvic hiatus. Trans-perineal ultrasound studies show that 15–20% of nulliparous women paradoxically contract the levator ani (co-activation) during pushing, narrowing the hiatus and slowing head descent. Consequently, about 20% of primigravidas experience a prolonged second stage, with higher rates of operative birth and perineal trauma.

**Methods and analysis:**

PURSUE is a single-centre, open-label, parallel-group RCT at Fondazione Policlinico A. Gemelli, Rome reported according to the SPIRIT 2013 and CONSORT 2010 guidelines. Nulliparous women between 28 + 0 and 37 + 0 weeks of gestation will be randomised 1:1 to midwife-led pushing training without ultrasound biofeedback or a midwife-led session combining theoretical instruction with real-time TPUS-guided pushing training. The primary endpoint is duration of the active second-stage of labour (minutes). Secondary outcomes include levator ani co-activation amplitude, spontaneous vaginal birth, perineal trauma, postpartum haemorrhage ≥ 500 mL, urinary/faecal incontinence at 6, 12 and 16 weeks postpartum and childbirth experience (CEQ-2). A sample of 228 (114 per arm) provides 80% power to detect a clinically meaningful reduction of 20 minutes(Cohen’s d = 0.37; α = 0.05, two sided). Allowing for 15% attrition, 268 women will be enrolled. The primary analyses uses multivariate linear regression adjusting for pre-specified covariates; secondary analyses are exploratory.

**Ethics and dissemination:**

The protocol is approved by Lazio Region Ethics Committee (Prot. 0000641/25) and registered on ClinicalTrials.gov (NCT07000240). Written informed consent is obtained at enrolment. An internal independent committee oversees safety. No formal interim analysis with pre-specified stopping rules is planned; accordingly, no alpha-spending adjustment is applied, and the pre-specified primary (confirmatory) analysis will be performed once, on the complete sample, after the end of follow-up. During the trial, preliminary results may be presented at scientific meetings for reporting and feasibility purposes; such presentations are exploratory and non-confirmatory, are not used to inform any decision to stop or modify the trial, and do not affect the pre-specified primary analysis or the control of the type I error rate. Results, the anonymised dataset and statistical code will be disseminated through peer-reviewed journals, conference presentations and an open-access repository within 12 months of completion.

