### Randomization, blinding and treatment allocation

Once eligibility is confirmed and informed consent is obtained, participants will be randomised (1:1) into one of two study arms: using a computer-generated random sequence (“randomizeR” package in R**).** Assignment to study groups will be managed through sealed, opaque and sequentially numbered envelopes accessible only to the research midwife, thereby maintaining allocation concealment until the moment of assignment.

Given the nature of the interventions, this study is designed as an open-label trial; both the participants and the researchers will be aware of the group assignments. While full blinding is not feasible due to the involvement of TPUS in one arm, outcome assessors will be blinded to group allocation when evaluating outcomes and analysing data. This approach aims to reduce assessment bias and ensure that the treatment allocation does not influence the collection and interpretation of results.

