#### Statistical analysis plan.

Data will be analysed on an intention-to-treat basis. Baseline demographics, obstetric history, and pregnancy-related variables will be summarised by treatment arm using means and standard deviations (or medians and interquartile ranges) for continuous variables and frequencies and percentages for categorical variables. Between-group balance will be described using standardised mean differences (SMD); formal significance testing of baseline differences will not be performed, consistent with established guidance for randomised trials [11]. Two time intervals will be recorded for every woman who reaches the second stage of labour:(i) the duration of the active pushing phase, defined as the interval in minutes from the first coordinated maternal expulsive effort accompanying a uterine contraction, whether spontaneous or initiated following midwifery coaching, until delivery;(ii) the duration of the total second stage, defined as the interval in minutes from confirmed full cervical dilatation until delivery. The duration of the active pushing phase is the primary endpoint, referred to throughout as the duration of active second stage of labour**,** as it corresponds to the phase targeted by the intervention and to the phase in which levator ani co-activation has been shown to operate [2,3], and is the interval from which the assumed standard deviation used in the sample size calculation was derived. The duration of the total second stage is reported as a secondary endpoint. Both intervals are recorded contemporaneously in the electronic partogram and extracted for analusis by a researched blinded to allocation.

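### The plan lets preliminary results be presented mid-trial without limiting them to pooled data, so its assurance that the primary analysis is unaffected rests on an unsecured assumption that nobody's behaviour changes

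*Protocol article*

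**What the plan says.** The permission and the assurance both stand in the Abstract of the protocol article, under Ethics and dissemination.

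- Permission: "During the trial, preliminary results may be presented at scientific meetings for reporting and feasibility purposes".
- Assurance on decisions: the presentations "are not used to inform any decision to stop or modify the trial".
- Assurance on inference: they "do not affect the pre-specified primary analysis or the control of the type I error rate".
- Analysis plan: "No formal interim analysis with pre-specified stopping rules is planned; accordingly, no alpha-spending adjustment is applied", and the "primary (confirmatory) analysis will be performed once, on the complete sample, after the end of follow-up".

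Three other statements bear on how results could act back on the trial.

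- Methods and analysis (Abstract): "PURSUE is a single-centre, open-label, parallel-group RCT".
- Randomization, blinding and treatment allocation: "both the participants and the researchers will be aware of the group assignments". Outcome assessors are to be blinded when they evaluate outcomes and analyse data.
- Statistical analysis plan: the primary interval begins at the first coordinated push with a contraction, whether the woman starts it herself or a midwife prompts it. "Both intervals are recorded contemporaneously in the electronic partogram", and a researcher blinded to allocation then extracts them.

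The section Pushing Training Program adds that the training midwives are not those who give care in labour.

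**The concern.** The permission carries no restriction to pooled or non-outcome data. One stated purpose is reporting, which is wider than feasibility. The text also goes out of its way to defend type I error, which pooled recruitment figures could not threaten. By-arm results are therefore a natural reading of what may be shown, although the text does not say so outright.

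If by-arm results were shown, people who recruit, train, attend births or take part could learn of an emerging difference while they can still influence the data. Possible routes are the enthusiasm with which training is delivered, the moment at which pushing is prompted or charted as begun, the timing of an operative delivery that ends the interval, and the answers of unblinded women to the CEQ-2 and ICIQ-SF. The assurance covers formal decisions to stop or modify the trial. It does not cover these informal routes. Once results are public they cannot be withdrawn, and no later analysis can identify or remove the bias.

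**Working it through.** **1. The plan's own figures.** Inputs from Sample size: difference 20 min, SD 53.5 min, two-sided α = 0.05, power 80%, 15% attrition.

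- n per arm = 2 × (1.960 + 0.842)² × 53.5² / 20² = 112.3, rounded up to 113. The t-test version gives 113.3, rounded up to 114, as stated.
- Enrolment = 228 / 0.85 = 268.2, against 268 stated. This is a rounding difference only.

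No stated figure is in dispute.

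**2. Does a look by itself inflate type I error?** Under the null, with 4 million simulated trials and a look at 25%, 50% or 75% of the information, the final test alone rejects in 0.050 of trials in each case. If nobody acts on the look and nobody behaves differently, the statement about type I error is correct.

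**3. What would unadjusted testing at a look do?** If success could be declared at either the look or the end, each at |z| > 1.96, the rate would be 0.091, 0.083 or 0.073 for a look at 25%, 50% or 75%. The Abstract excludes this use, so these figures do not describe this trial.

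**4. What if behaviour changes?** Assume no true effect, and a shift of b minutes in the recorded between-arm difference among the fraction f of women who deliver after a presentation. Neither b nor f comes from the documents.

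- SE = 53.5 × √(2/114) = 7.09 min
- Overall bias = f × b, and m = f × b / SE
- P(reject) = Φ(m − 1.96) + Φ(−m − 1.96)

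| Assumed shift b | f = 0.25 | f = 0.50 | f = 0.75 |
|---|---|---|---|
| 2 min | 0.051 | 0.052 | 0.055 |
| 5 min | 0.054 | 0.064 | 0.083 |
| 10 min | 0.064 | 0.109 | 0.185 |

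For b = 5 and f = 0.50, the overall bias is 2.5 min, which is 2.5 / 20 = 12.5% of the target difference, and m = 2.5 / 7.09 = 0.35. The table shows only that the assurance depends on unchanged behaviour. It does not estimate what would happen.

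**5. Do the stated safeguards secure unchanged behaviour?**

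- Separate trainers: the labour-ward midwives are not said to be blinded, and a woman who knows her arm can tell them.
- Blinded extraction: the extractor copies times that are already charted, so an influence at the bedside is carried through.
- Blinded analysis: this protects evaluation, not the conduct of labour or women's own answers.

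**6. How long is the exposure?** Enrolment runs to 31/07/2026, from 28+0 weeks. If the last woman enrols at 28+0 and delivers at 40+0 (an assumption), she delivers 12 weeks later, on 23 October 2026, and reaches the 16-week contact on 12 February 2027.

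**The case against.** The strongest case for the plan is that it is open about the presentations, fixes a single confirmatory analysis on the complete sample, and ties no decision to what is shown. On those terms its type I error statement is right, as step 2 confirms. The text nowhere says that outcomes by arm will be shown, and the results might be pooled. Allocation is concealed in sealed envelopes, so a change in who enrols would not by itself bias the comparison. Differential charting requires labour-ward staff to learn a woman's arm, a risk that any open-label trial carries. The questionnaire outcomes are secondary and labelled exploratory. A journal article may also leave data-access rules to the full protocol.

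Much of this stands. It rules out three stronger readings that a reader might infer:

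- That type I error rises to about 8.3%. This requires a claim of success at an unadjusted mid-trial look, which the plan excludes. It is not a ceiling either, since a look at 25% information would give 9.1%.
- That a 5-minute charting shift would amount to 25% of the 20-minute target. The 5 minutes is an assumption, and only women delivering after a presentation could be affected.
- That staff and participants will be exposed to by-arm results, or that looks would go unreported. Exposure is possible, not certain, and the presentations are disclosed.

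It does not answer the point itself. The article states a permission and an unconditional assurance. The objection here is to those two statements, not to details left out.

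**Conclusion.** The point holds as a risk of operational bias. The plan permits mid-trial presentation of results that are not limited to pooled data, and then states without condition that the primary analysis and type I error are unaffected. That statement is true only if recruiters, trainers, labour-ward staff and participants behave as they would have done without the results. The safeguards described make this more likely but do not secure it, because the start of the primary interval is charted live and may follow coaching.

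The size of any bias cannot be derived from the documents. Under the assumed shifts of 2 to 10 minutes, the false-positive rate ranges from 0.051 to 0.185. If behaviour does not change, it is 0.050. The type I error statement is therefore incomplete, not false, and needs a condition rather than removal.

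**What to change.** Replace the permission with wording such as: until follow-up of the last participant is complete and the database is locked, only pooled, non-comparative information (recruitment, baseline characteristics, adherence, feasibility) may be presented, and outcome data by arm stay within the committee that oversees safety.

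Keep the commitment to one confirmatory analysis on the complete sample. Make the assurance about the primary analysis and type I error conditional on the restriction above.

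The cost is a few lines of text, and conference abstracts with by-arm results must wait until follow-up ends. The sample size (228 analysed, 268 enrolled) and alpha of 0.05 do not change. If pooled data were always intended, the edit only states that intention.

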**Trial registration:**

ClinicalTrials.gov NCT07000240

## Introduction

Fetal head descent during the active second stage of labour is influenced, among other factors, by maternal expulsive force. Optimal synergy occurs when abdominal‐muscle contraction is synchronised with relaxation of the levator ani muscle (LAM), which widens the pelvic hiatus and reduces soft-tissue resistance [1]. The pivotal role of the LAM in labour progress is well documented [2].

Trans-perineal ultrasound (TPUS) studies have shown that 15–20% of nulliparous women display paradoxical LAM co-activation, a contraction instead of the expected relaxation, during pushing [2, 3]. This phenomenon can be quantified on TPUS by tracking levator-hiatus diameter changes during the Valsalva manoeuvre [3]. Co-activation is associated with a higher fetal head station at term and a longer active pushing phase, increasing the likelihood of operative vaginal delivery, severe perineal tears, pelvic-floor damage and fetal distress [1,3,4]. These observations underscore the need for targeted educational interventions, such as real-time ultrasound biofeedback, to correct LAM co-activation and optimise pushing.

Pilot studies indicate that TPUS-guided, real-time visual biofeedback can shorten the second stage of labour by enhancing maternal neuromuscular coordination [5,6]; however, none has explicitly focused on promoting levator ani relaxation. Midwives are ideally placed to integrate TPUS into antenatal education and labour support, using visual demonstrations of pelvic-floor anatomy, fetal positioning and effective pushing techniques [7]. Combining TPUS feedback with midwife-led instruction therefore offers a personalised, evidence-based strategy to improve labour outcomes [8].

Therefore, the PURSUE (Pushing Using Real-time Sonographic Ultrasound Education) trial will evaluate whether a midwife-led, 60-minute session, combining an antenatal theoretical lesson on pushing with real-time TPUS-guided training, can shorten the second stage of labour and reduce the incidence of LAM co-activation in healthy nulliparous women compared with midwife-led pushing training without ultrasound biofeedback.

### Study hypothesis

Integrating real-time TPUS-guided training into routine midwife-led antenatal classes is expected to shorten the average duration of the second stage of labour by at least 20 minutes.

## Materials and methods

### Study design and duration

This non-profit, single-centre, open-label randomised controlled trial (RCT) will be conducted at the Fondazione Policlinico Universitario Agostino Gemelli IRCCS, Rome, Italy. The protocol follows the SPIRIT 2013 statement; a completed SPIRIT checklist is provided as Supplementary File 2. Trial reporting will adhere to the CONSORT 2010 statement for parallel-group RCTs; a preliminary CONSORT checklist is provided as Supplementary File 1. SPIRIT schedule of enrolment, interventions and assessments provided in Fig 1. The enrolment period is from 18/07/2025–31/07/2026.

**Fig 1 pone.0352315.g001:**
[figure not shown]
SPIRIT schedule of enrolment, intervention and assessment for the PURSUE trial.

### Objectives

#### Primary.

To determine whether integrating real-time transperineal ultrasound-guided (TPUS) training into routine midwife-led antenatal classes shortens the average duration of the second stage of labour by ≥ 20 minutes compared with midwife-led pushing training without ultrasound biofeedback. In recognition of the multiple maternal, fetal and intrapartum factors that influence second-stage duration, overall efficacy will also be assessed using a composite maternal-neonatal outcome considering core endpoints recommended for obstetric trials [9] and previously used in large cohort studies and randomised controlled trials evaluating prolonged second-stage management [4,10].

*Secondaries:*

To quantify the proportion of women who demonstrate levator ani muscle (LAM) co-activation—defined as an anteroposterior diameter change (APD) < 0 mm—at two time-points: (i) during the TPUS-guided training session, and (ii) at birth, where an intrapartum sonographic assessment is feasible within routine clinical care.To compare postpartum maternal satisfaction between the control and TPUS-guided intervention arms, as measured by the Childbirth Experience Questionnaire 2 (score range 0–100).To quantify the difference of prevalence in 1st-, 2nd-, 3rd- and 4th-degree perineal tears between the control and the TPUS-guided intervention arms.To measure the difference in total postpartum blood loss (mL) within 24 hours of delivery between the control and the TPUS-guided intervention arms.To compare the rates of spontaneous vaginal birth, operative vaginal birth and unplanned caesarean sections between the control and the TPUS-guided intervention arms.To evaluate the prevalence of stress or urge urinary incontinence at 6, 12, 16 weeks postpartum between the control and the TPUS-guided intervention arms, defined as an International Consultation on Incontinence Questionnaire-Urinary Incontinence Short Form (ICIQ-SF) score ≥ 6.To compare the proportion of women that require pharmacological augmentation during the active second-stage of labour between the control and TPUS-guided intervention arms.To quantify the association between persistent fetal malposition (non-occiput-anterior at full cervical dilatation and/or at delivery) and the length of the second stage of labour (minutes), and to test whether this association differs between the control and TPUS-guided intervention arms. This association is observational in nature and is not interpreted as a randomised comparison.

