#### Setting.

This single-center study will be conducted at Fondazione Policlinico Universitario Agostino Gemelli IRCCS Rome, an academic private tertiary-level hospital located in central Italy, with over 4,000 births per year. Childbirth care is characterised by continuous one-to-one intrapartum support provided by registered midwives under the supervision of senior midwives and obstetricians. Second-stage management follows physiological principles. In nulliparous women with epidural analgesia, delayed pushing is practised until the urge to push is felt or the fetal head reaches the pelvic floor; active pushing is then maternal-led, with verbal coaching by attending midwives. Practitioners do not routinely use ultrasound during the pushing stage to assess fetal station or perineal status. Intrapartum care is identical for both study arms; only the antenatal training component differs. In 2025 the hospital recorded an epidural analgesia rate of 72%, a primary cesarean section rate of 19%, and an operative vaginal delivery rate of approximately 11%, performed by vacuum extraction (Kiwi Cup).

Although a dedicated pelvic floor outpatient unit is available, no standardized postpartum pelvic floor rehabilitation protocol is in place. Rehabilitation sessions are therefore not scheduled as part of routine care, and attendance at external pelvic floor rehabilitation is not systematically recorded. All women are nonetheless advised at discharge of the importance of pelvic floor evaluation in the postpartum period. Attendance at pelvic floor rehabilitation will be recorded at the16 weeks follow-up contact. Should the rate of rehabilitation uptake exceed 10% in either arm, it will be included as a covariate in exploratory sensitivity analyses for pelvic-floor related outcomes.

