The primary endpoint will be analysed using multivariable linear regression, with treatment arm as the main predictor. The model will be adjusted for pre-specified baseline covariates only, that is, variables measured before randomisation: maternal age, body mass index at enrolment, gestational age at randomisation, maternal height, and sonographic estimated fetal weight at the last available third-trimester scan. Consistent with ICH E9, no post-randomisation variable is included in the confirmatory model, since conditioning on variables measured after allocation may invalidate the randomisation-based causal interpretation of the treatment effect. This applies in particular to fetal head position at full cervical dilatation, epidural analgesia and gestational age at delivery, which are potential intermediate variables on the causal pathway between the intervention and the primary endpoint. Their distribution across arms will be reported descriptively, and epidural analgesia and fetal head position will be examined as potential effect modifiers through interaction terms, as exploratory analyses. The primary result will be reported as an adjusted mean difference with 95% confidence interval; the p-value will be provided as secondary inferential information. If the residuals of the linear model indicate substantial departure from normality, a bootstrap confidence interval will be computed. Women who do not reach the active second stage (e.g., caesarean delivery before full dilatation) will not contribute to the primary analysis but will be retained in the ITT population for all secondary outcomes. For clarity, the primary estimand may therefore be summarised as the difference in adjusted mean duration of the active pushing phase between arms among randomised nulliparous women reaching the active second stage, with operative vaginal delivery and second-stage caesarean section handled under a treatment-policy strategy as delivery events at the observed time. The number of women contributing to each analysis, with the corresponding denominators and reasons for non-contribution, will be reported by arm in the CONSORT flow diagram, and the baseline characteristics of women not reaching the active second stage will be compared between arms using standardised mean differences. Sensitivity analyses will include multiple imputation under the missing-at-random assumption and inverse probability weighting to assess the robustness of the primary estimate to differential attrition, applied to observations that are missing rather than undefined, such as incomplete partogram times or non-returned questionnaires; where an imbalance is observed in the proportion of women reaching the active second stage, inverse probability of selection weights will be applied accordingly. Time to spontaneous vaginal birth from the onset of active pushing will additionally be described using cumulative incidence functions, with operative vaginal delivery and second-stage caesarean section treated as competing events rather than as censored observations, and compared between arms using Gray's test. This analysis is supportive and exploratory.

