
Mode of delivery (spontaneous vaginal birth vs. operative vaginal or caesarean), perineal tears (≥ 3rd degree vs. none/1st–2nd degree), postpartum haemorrhage (≥ 500 mL vs. < 500 mL), and need for pharmacological augmentation during the active second stage will be analysed using logistic regression with the same set of pre-specified baseline covariates. Results will be reported as adjusted odds ratios with 95% CIs, accompanied by absolute risks and risk differences by arm to facilitate clinical interpretation. For endpoints with a low expected number of events, Firth's penalised-likelihood estimation will be used. Third- and fourth-degree perineal tears will be analysed among all women reaching the second stage, with caesarean deliveries counted as no injury, and additionally among women delivering vaginally. Mode of delivery is also addressed within the competing-risks analysis described above. Total postpartum blood loss (mL) and maternal satisfaction (CEQ-2 score) will be analysed using multivariable linear regression as described for the primary endpoint, reporting adjusted mean differences with 95% CIs, with bootstrap confidence intervals reported for blood loss in view of its expected skewness. Urinary incontinence (ICIQ-SF score ≥ 6) will be assessed at 6 weeks, 12 weeks and16 weeks postpartum. The outcome will be modelled using mixed-effects logistic regression with a random intercept for participant and fixed effects for treatment arm, time point, and their interaction, adjusted for the same baseline covariates. This approach accounts for within-subject correlation across repeated assessments and allows estimation of the treatment effect trajectory over time and makes use of all available observations under a missing-at-random assumption. Both the interaction term and the adjusted treatment effect at each time point will be reported. Attendance at postpartum pelvic floor rehabilitation, a post-randomisation variable, will be summarised descriptively by arm and, where uptake exceeds 10% in either arm, included in sensitivity analyses for pelvic floor–related outcomes as described above. Pre-specified subgroup analyses will examine potential effect modification by: (i) Within-arm analysis of levator ani function (intervention arm only); (ii) gestational age at intervention (28–34 weeks vs. 35–37 weeks); and (iii) epidural analgesia (yes/no). Subgroup (ii) and subgorup (iii) are defined by post-randomisation variables and are reported as exploratory only. Subgroup effects will be estimated via interaction terms in the regression models and reported as stratum-specific effect estimates with 95% CIs. All secondary, subgroup, and repeated-measures analyses are regarded as exploratory and hypothesis-generating. The trial is powered exclusively on the primary endpoint. Results of secondary analyses will be reported as point estimates with 95% confidence intervals without correction for multiplicity and should be interpreted in the context of the overall pattern of findings rather than as confirmatory evidence. All analyses will be conducted using R (R Foundation for Statistical Computing) and STATA (StataCorp LLC).

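### The mode-of-delivery objective names three rates, but no stated analysis gives a between-arm estimate for operative vaginal birth or unplanned caesarean in all randomised women

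*Protocol article*

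**What the plan says.** The secondary objectives of the Protocol article (under Objectives) include: "To compare the rates of spontaneous vaginal birth, operative vaginal birth and unplanned caesarean sections between the control and the TPUS-guided intervention arms". That is three rates, with caesarean limited to unplanned sections.

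The Statistical analysis plan section specifies one logistic regression for this outcome, with two levels: "Mode of delivery (spontaneous vaginal birth vs. operative vaginal or caesarean". Its odds ratios are to be "accompanied by absolute risks and risk differences by arm to facilitate clinical interpretation". The word unplanned is not carried over.

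On the population, women who do not reach the active second stage, for example because of a caesarean before full dilatation, "will not contribute to the primary analysis but will be retained in the ITT population for all secondary outcomes".

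The same section adds: "Mode of delivery is also addressed within the competing-risks analysis described above". The event of interest there, and its starting point, are given as: "Time to spontaneous vaginal birth from the onset of active pushing will additionally be described using cumulative incidence functions". The remaining two modes enter only as competitors to that event: "with operative vaginal delivery and second-stage caesarean section treated as competing events rather than as censored observations, and compared between arms using Gray's test". It is labelled supportive and exploratory.

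The Setting section gives the hospital's 2025 figures: "a primary cesarean section rate of 19%, and an operative vaginal delivery rate of approximately 11" per cent.

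**The concern.** The objective and its analysis do not match. The article does not leave the method open for a fuller document to settle. It states a method, and that method covers one of the three rates the objective names.

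Two things are at stake. First, operative vaginal birth and caesarean are different outcomes for the woman, and training in pushing could move them by different amounts or in opposite directions. A single merged event weakens a change in one of them and can cancel opposing changes completely. Second, the objective concerns unplanned caesarean, while the analysis counts caesarean without qualification among all randomised women. Randomisation takes place between 28+0 and 37+0 weeks, so a reason for a planned section can arise afterwards. Such births would enter the merged event as written.

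**Working it through.** **1. Which rate is covered by which stated analysis**

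| Rate named in the objective | Logistic model, all randomised women | Competing-risks analysis, from onset of pushing |
|---|---|---|
| Spontaneous vaginal birth | Yes, with odds ratio and risk difference | Yes, as the event of interest, with Gray's test |
| Operative vaginal birth | Only inside the merged event | A competing event; no comparison of it is stated |
| Unplanned caesarean | Only inside the merged event, with any other caesarean | Second-stage sections only, as a competing event; earlier sections are outside |

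Neither column gives a between-arm estimate for the second or third row in all randomised women.

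**2. Planned caesareans**

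Three statements combine. The Sample size section expects some caesareans before labour. The Statistical analysis plan keeps women with a caesarean before full dilatation in the secondary analyses. The merged category says caesarean without qualification. The exclusion criteria remove only contraindications to vaginal delivery that are known at entry. Nothing removes a later planned section from the merged event, although no sentence states that it is counted.

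**3. Illustration of what merging does**

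The plan gives no figure of its own for this outcome, so there is none to reproduce. Inputs are 11% operative vaginal and 19% caesarean (Setting) and 134 women per arm (Sample size). The assumptions are that these rates apply to trial women and share a denominator. The effects below are hypothetical.

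Merged event: 0.11 + 0.19 = 0.30, of which 0.19/0.30 = 63% is caesarean of any kind. Expected counts per arm are 134 × 0.11 = 14.7 and 134 × 0.19 = 25.5.

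*Operative vaginal birth halved (11% to 5.5%), caesarean unchanged:*
- Operative vaginal OR = (0.055/0.945)/(0.11/0.89) = 0.47.
- Merged OR = (0.245/0.755)/(0.30/0.70) = 0.76.
- The risk difference is 5.5 points either way, but its precision is not the same. The 95% half-width is 1.96 × √[(0.11×0.89 + 0.055×0.945)/134] = 6.6 points for operative vaginal birth alone. For the merged event it is 1.96 × √[(0.30×0.70 + 0.245×0.755)/134] = 10.6 points.
- Power at two-sided 0.05 (normal approximation) is about 37% for operative vaginal birth alone and 17% merged.

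*Opposite 4-point shifts (operative vaginal 11% to 7%, caesarean 19% to 23%):*
- Merged rate = 0.07 + 0.23 = 0.30 against 0.30, so OR = 1.00 and the risk difference is 0.
- Separately, the ORs are (0.07/0.93)/(0.11/0.89) = 0.61 and (0.23/0.77)/(0.19/0.81) = 1.27.

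**4. If the two rates do not share a denominator**

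The Setting section does not give the denominators. If the 11% were a share of vaginal births, operative vaginal birth would be 0.11 × 0.81 = 8.9% of all births, and the merged event 8.9% + 19% = 27.9%. Halving operative vaginal birth then gives an OR of (0.04455/0.95545)/(0.0891/0.9109) = 0.48 and a merged OR of (0.23455/0.76545)/(0.2791/0.7209) = 0.79. The pattern is the same.

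**The case against.** The strongest reply has four parts.

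*The objective is largely met.* The abstract lists spontaneous vaginal birth as the secondary outcome, and the binary contrast estimates exactly that, with risk differences. This stands. A reader might infer that the objective is not answered at all, and the text does not support that. One of its three rates is answered; two are not.

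*The competing-risks analysis covers the rest.* It names operative vaginal delivery and second-stage caesarean separately. A reader might infer that the two are pooled into one cause, but the article does not say so. A shift from vacuum to second-stage caesarean also happens after pushing begins, so the women concerned are in that analysis. This stands in part. The only stated event of interest is spontaneous birth, no comparison of the other two modes is promised, and caesareans before pushing are outside it.

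*The dilution is unproven.* A reader might infer that caesareans before pushing dominate the merged event. The documents do not support this, because the 19% is not split into planned, first-stage and second-stage sections. The 63% refers to all caesareans. It is likewise an inference, though one that nothing contradicts, that planned sections are counted.

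*The consequence is small.* All secondary analyses are declared exploratory and uncorrected for multiplicity. With about 15 operative vaginal births expected per arm, even a halving would be detected only about 37% of the time, so separate estimates will rarely settle anything. By-arm counts are routine and may be reported anyway. This limits the weight of the point. It does not remove the mismatch, because the article states a particular analysis that differs from its own objective. For severe perineal tears, the same section does say how caesareans are counted and which denominators are used.

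**Conclusion.** The point holds in a limited form. Followed as written, the plan estimates spontaneous vaginal birth by arm but produces no between-arm estimate of operative vaginal birth or of unplanned caesarean in all randomised women, although both are named in the objective. Planned pre-labour caesareans appear to fall into the merged event. This is an ambiguity to be resolved, and its size cannot be derived because no count of such births is given.

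The figures (OR 0.47 against a merged 0.76; 30% against 30% under opposite 4-point shifts) are an illustration. They rest on hospital-wide 2025 rates applying to trial women, on the two rates being additive, and on hypothetical effects. The primary endpoint, the sample size and the confirmatory inference are untouched. The correction is worth making because it costs little and brings the objective and the analysis into line.

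**What to change.** In the Statistical analysis plan section:

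- Report operative vaginal birth and unplanned caesarean separately by arm in all randomised women, each with a risk difference and 95% CI.
- Define unplanned, and show planned pre-labour caesareans as their own category.
- Keep the merged contrast as a summary, saying how planned sections are counted in it.
- In the competing-risks analysis, show the cumulative incidence of operative vaginal delivery and of second-stage caesarean separately.

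The cost is a few more exploratory estimates with few events and wide intervals. On the illustrative rates, the 95% half-width for operative vaginal birth is 6.6 points. The data also need a check: the Data collections section describes mode of birth only as vaginal or caesarean, so the extraction form should be confirmed to record operative delivery and whether a caesarean was planned. Sample size and primary analysis do not change.
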